#### Blinding

The primary investigator ([name]) will be blinded to allocation and will not participate in the randomization of participants. The statistical analysis will only be performed on allocation codes; thus, the data analysts will be blinded concerning intervention allocation. Blinding of patients, surgeons, and nurses (healthcare providers) will not be possible due to the nature of the intervention.

### Sample size calculation and statistical procedures

To our knowledge, there are no anchor-based minimum clinically important differences (MCID) specifically for physical activity in knee patients. As a substitute, we use an MCID for steps per day, derived from chronic obstructive pulmonary disease research, corresponding to a change of approximately 17%–35% [31]. Applying a 17% threshold to total accelerometer counts per day, based on a previous study of TKA patients [9], yields an anticipated between-group difference in change score of 50,500 activity counts per day. This expected difference is further supported by findings from Van der Walt et al. (2018) [25], who demonstrated a 17% increase in daily step count in the feedback group compared to the non-feedback group after six months. To achieve 80% statistical power (β = 0.80) and detect statistically significant differences at a two-tailed α level of 0.05, assuming a standard deviation of 101,000 counts per day before and after the intervention [9] a sample size of 62 participants per group is estimated. To account for potential dropouts, we use a rate of 20% based upon evidence from a systematic review showing that dropout rates in RCTs on physical activity are within this percentage [32]. Consequently, we will include a sample of 150 patients in total. When appropriate, all outcome measures will be checked for Gaussian distribution using QQ-plots and parametric statistical and/or non-parametric analyses.

No a priori sample size calculation is made for the cohort study. However, based on a total sample of approximately 1,400 annual knee replacement procedures for OUH and Vejle hospitals, it is reasonable to expect an inclusion of 200 patients, which is acceptable for the current statistical analysis plan on predictive regression models [30].

The main comparative analyses between groups will be performed using an intention-to-treat analysis. Between-group mean differences and 95% confidence intervals will be estimated with a linear regression model. The patient’s baseline score is entered as a covariate and adjusted for potential baseline differences (age, sex, BMI). In addition to the intention-to-treat analysis, a per-protocol analysis will be conducted on patients adhering to the intervention (using the patient app for 5 out of 7 days in a week or > 70% of the available days.

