#### Randomization

Randomization is performed internet-based using REDCap Randomize, allocated 1:1. Randomization occurs after baseline measurements on the day of surgery. The randomization is performed in blocks of 2, 4, and 6. No stratifications are applied to the randomization, and the primary investigator is blinded regarding the permuted blocking strategy. A data manager, with no clinical involvement in the trial, prepares the randomization sequence. The allocation is concealed in a password-protected computer file that is only accessible to relevant personnel.

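### On the protocol's own figures, 150 patients with 20% dropout leave 60 per group, fewer than the 62 it says it needs, and give about 77.5% rather than 80% unadjusted power (minor; wording only)

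*Protocol article*

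**What the plan says.** All the inputs are in the Protocol article, under Sample size calculation and statistical procedures.

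- Effect: a 17% threshold applied to total daily counts "yields an anticipated between-group difference in change score of 50,500 activity counts per day".
- Spread: "assuming a standard deviation of 101,000 counts per day before and after the intervention".
- Error rates: "To achieve 80% statistical power (β = 0.80"), and the aim to "detect statistically significant differences at a two-tailed α level of 0.05".
- Result before dropout: "a sample size of 62 participants per group is estimated".
- Dropout: "To account for potential dropouts, we use a rate of 20"%, supported by a systematic review whose rates are said to lie within that figure.
- Result after dropout: "Consequently, we will include a sample of 150 patients in total".

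Under Randomization, allocation is 1:1, so 150 means 75 per group. The inflation formula is not printed, and no other section gives a different allowance or another reason for 150. The same section plans the main analysis as a linear regression with the baseline score as a covariate, also adjusted for age, sex and BMI.

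**The concern.** The total is presented as following from 62 per group and 20% dropout, and a reader can check that in one line. Taking 20% from 150 leaves fewer than the 124 that the same paragraph requires. This is the only justification given for the size of the randomised trial. If it does not hold on its own inputs, the power and the dropout tolerance quoted from it are both slightly too favourable. The label attached to the power is also wrong: β is the type II error, so 80% power means β = 0.20.

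**Working it through.** **Inputs** (all from the sample size section, with 1:1 allocation from Randomization): difference 50,500; SD 101,000; two-sided α 0.05; power 0.80; dropout 20%. The standardised difference is d = 50,500/101,000 = 0.50.

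**1. The figure before dropout.**
Normal approximation: n per group = 2(1.960 + 0.842)²/0.50² = 62.79, which rounds up to 63.
Two-sample t-test: n = 63.77, which rounds up to 64.
The printed 62 is 62.79 truncated. At 62 per group, power is 79.5% (normal) or 78.9% (t-test). A one-sided test would need 50 per group, so sidedness does not explain the 62.

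**2. The figure after dropout.**
Multiplying: 62 × 1.2 = 74.4, rounded up to 75 per group, gives 150. This reproduces the printed total exactly.
Dividing, which is what keeps n after a 20% loss:

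| Needed per group | Divided by 0.8 | Randomised per group | Total |
|---|---|---|---|
| 62 (as printed) | 77.5 | 78 | 156 |
| 63 (normal) | 78.75 | 79 | 158 |
| 64 (t-test) | 80.0 | 80 | 160 |

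**3. What 150 delivers at 20% dropout.**
150 × 0.8 = 120, or 60 per group.
Normal: power = Φ(0.50 × √(60/2) − 1.960) = Φ(2.739 − 1.960) = 78.2%.
t-test (noncentral t, 118 degrees of freedom, noncentrality 2.739): 77.5%.

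**4. How much dropout 150 can absorb.**
To keep 62 per group: 1 − 124/150 = 17.3%.
To keep 63 per group: 1 − 126/150 = 16.0%.
To keep 64 per group: 1 − 128/150 = 14.7%.

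**5. The planned model.** If 101,000 is the SD at a single time point, adjusting for baseline reduces the residual SD to 101,000 × √(1 − ρ²), where ρ is the correlation between baseline and 12 weeks. The effective standardised difference is then 0.50/√(1 − ρ²). The documents give no ρ, so the values below are assumptions. Power is by t-test with 60 per group.

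| Assumed ρ | 0.50/√(1 − ρ²) | Power |
|---|---|---|
| 0 | 0.500 | 77.5% |
| 0.25 | 0.516 | 80.1% |
| 0.3 | 0.524 | 81.3% |
| 0.5 | 0.577 | 88.0% |

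By the normal approximation the 80% mark is reached at a ρ of about 0.21.

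**The case against.** **The shortfall is small.** It is 1.8 points by the normal approximation and 2.5 by the t-test. The truncation of 62.79 to 62 accounts for about half a point and would not be worth raising alone. This stands, and it is why the point is minor.

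**The ×1.2 step is inferred.** No formula is printed, and 150 could be a rounded target. The 20% can also be read as an upper bound, since the cited review is said to show rates within it. This stands as far as the cause goes. The conflict does not depend on the cause: however 150 was reached, 20% loss leaves 60 per group. If a lower dropout was meant, the text should say so, because it takes 20% and draws 150 from it.

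**The planned analysis may recover the power.** A reader might infer that the trial is underpowered and must recruit more. The documents do not support that. The main analysis is baseline-adjusted, and under the single-time-point reading of the SD a correlation of about 0.25 is enough for 80% with 60 per group. On the other side, the section does not use the adjustment to justify 150 and states no correlation, so the adjustment does not rescue the derivation as printed.

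**The SD.** A reader might also infer that 101,000 was wrongly used as the SD of a change score, and that true power could be far lower. The text pairs an SD before and after the intervention with a difference in change score, so the wording is loose. But d = 0.50 arises equally from comparing 12-week levels with that SD, which is conservative for the adjusted model. A large loss of power would belong to an unadjusted change-score test, which is not the planned main analysis. What the SD describes depends on a cited study that is not at hand.

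**Conclusion.** The derivation is wrong as written, and the consequence is minor. At the stated dropout rate, 150 patients leave 60 per group against the 62 required. On the stated inputs, unadjusted power is then 77.5% (t-test) or 78.2% (normal), not 80%. The dropout step is the main error; the truncation adds to it, and the β label is a slip of notation beside an explicit 80%.

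The result assumes the unadjusted two-sample comparison that reproduces the printed 62 to within truncation, and equal loss in both groups. It does not establish that the trial will miss 80% power under its planned regression, because that depends on a correlation the documents do not give.

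**What to change.** Keep 150 and restate the paragraph along these lines: *64 participants per group are needed for 80% power (1 − β = 0.80) at a two-sided 5% level; 150 randomised allows for up to 14.7% dropout; at 20% dropout, 60 per group remain and unadjusted power is about 77.5%.* The power has to be restated together with the change from 62 to 64; otherwise the mismatch with 150 widens.

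The sponsor may add, as an explicit assumption, that if 101,000 is the SD at a single time point, the baseline-adjusted regression reaches 80% with 60 per group when the baseline-to-12-week correlation is at least about 0.25 (81% at 0.3, 88% at 0.5). That correlation should not simply be borrowed from the study cited for the SD. The Background describes that study as comparing three weeks after surgery with the preoperative level, whereas the endpoint here is 12 weeks.

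The cost is wording only. The quoted unadjusted power falls by about 2.5 points, and no patients, visits or analyses change.

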### Compliance

Both groups will have an app installed on a dedicated tablet (the intervention group) or their smartphone (the control group). For the control group, the app does not provide motivational feedback but is solely used to transfer data from the activity tracker to a central research database. To prevent data loss, weekly SMS messages will be sent to both groups with the message "Have you opened your SENS app this week?”. Furthermore, the researchers can verify proper attachment by following the skin temperature evaluated by the sensor via a web module. If the temperature fluctuates over an extended period, a project manager will call the patient to solve potential issues. A standard for adherence to app interventions has yet to be established. However, based on patient feedback, an adherence rate of 70%, meaning that the intervention group will use the app along with motivational feedback for 5 out of 7 weekdays, seems reasonable.

All patients will receive oral and written information on how to attach the sensor, use the app (without a tablet), and use the tablet with motivational feedback. Moreover, all patients will receive a link to a YouTube video presenting the project and providing instructions on how to use the equipment.

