### Study design

Prior to this RCT, a qualitative study was conducted including 10 TKA/mUKA-patients. Integrating qualitative research before the RCT strengthens the study design by understanding our population and their perspectives. Furthermore, the qualitative study helped optimize the app for the population and their specific needs. This approach facilitates a more comprehensive and well-informed methodology for conducting rigorous and impactful research.

Only a few exclusion criteria will be employed to improve external validity and generalizability. However, the study may potentially be affected by selection bias. An exclusion criterion of “do not own a smartphone” will be used since the use of a smartphone is necessary for the intervention. Furthermore, the trial is based on patients volunteering for a physical intervention, which can also be a cause of selection bias. The accelerometer used in this trial has a maximum memory capacity of 7–14 days. To prevent data loss resulting from a full memory, it is required to establish a weekly data transfer connection to a smartphone using the dedicated application. Therefore, we decided to send a weekly SMS reminder to patients in the intervention and control groups. This approach may introduce attention bias. Moreover, all patients, whether in the intervention or control group, will be aware of wearing the accelerometer, which also may introduce attention bias. However, using their own smartphones to transfer data should minimize the risk of bias in the control group, resulting in more accurate PA levels for comparison.

Public access to the current protocol paper and prior registration on ClinicalTrials.gov will guarantee transparency regarding the implemented methods and definitions of outcome measures.

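### The supplementary per-protocol analysis selects on feedback-app use, which only the intervention arm can show, so it is not a randomised comparison and can be biased, probably toward benefit

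*Protocol article*

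**What the plan says.** In the protocol article, the section Sample size calculation and statistical procedures makes intention-to-treat the main comparison. It uses linear regression adjusted for baseline score, age, sex and BMI. It then states that "a per-protocol analysis will be conducted on patients adhering to the intervention (using the patient app for 5 out of 7 days in a week". The alternative way to qualify is use on more than 70% of available days.

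The Compliance section gives the standard behind that rule: "an adherence rate of 70%, meaning that the intervention group will use the app along with motivational feedback for 5 out of 7 weekdays". The standard is tied to the intervention group and to use with feedback. Of the controls the same section says: "For the control group, the app does not provide motivational feedback but is solely used to transfer data". The Discussion (Study design) explains how often contact is needed: because of the sensor's memory limit, "it is required to establish a weekly data transfer connection to a smartphone using the dedicated application".

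The article does not say which controls enter the per-protocol set.

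**The concern.** A per-protocol comparison keeps the protection of randomisation only if patients are selected in the same way in both arms, or on something unrelated to outcome. Neither is secured here. The criterion is use of a feedback app that one arm does not have. Use of that app is also close to the outcome, since it shows patients their own steps, active minutes and goals. Patients who are recovering well or are strongly motivated may both open it more and move more. Those with pain or complications may do less of both. Adjustment for baseline activity, age, sex and BMI does not remove differences in recovery or motivation that arise after surgery.

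At stake is how the supplementary result is read: it could suggest a benefit of the app that comes from who was kept in the analysis. A second, separate matter is that the weekly criterion can be read in several ways, and these could give very different analysis sets.

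**Working it through.** **Inputs from the protocol article.** Target difference 50,500 counts/day; SD 101,000; two-sided alpha 0.05; power 80%; 62 per group; 12 weeks of intervention, or 84 days.

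**The plan's own figure.** n per group = 2 × (1.960 + 0.842)² × (101,000 / 50,500)² = 62.8. The stated 62 is reproduced to within one patient on the normal approximation, so 50,500 and 101,000 are the right scale for judging bias.

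**Assumed inputs.** The article gives neither the share who adhere (p) nor the correlation (r) between propensity to adhere and the week-12 outcome. Both are varied below. There is no true effect throughout.

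**Bias if non-adherers are dropped from the intervention arm only.** With a normal propensity to adhere, the adherers' mean is shifted by r × φ(c)/p SDs, where c = Φ⁻¹(1 − p).
- For p = 0.7, φ(c)/p = 0.497.
- With r = 0.3, the bias is 0.3 × 0.497 = 0.149 SD, and 0.149 × 101,000 ≈ 15,000 counts/day, or 30% of 50,500.
- With 62 controls and 0.7 × 62 ≈ 43 adherers, SE = 101,000 × √(1/62 + 1/43.4) ≈ 20,000. A two-sided 5% test then rejects about 11.7% of the time.

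**With baseline adjustment.** Assume a baseline to follow-up correlation of 0.5. The residual SD is 101,000 × √(1 − 0.25) ≈ 87,500, and 0.149 × 87,500 ≈ 13,000. A simulation (4,000 runs per setting, 62 per arm, adjusting for baseline score only) agrees. Each cell gives bias in counts/day, its share of 50,500, and type I error:

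| Link between adherence and outcome | 60% adherent | 70% adherent | 80% adherent |
|---|---|---|---|
| None, or only through baseline activity | about 0; 0.05 | about 0; 0.05 | about 0; 0.05 |
| Residual correlation +0.3 | +17,200 (34%); 0.16 | +13,100 (26%); 0.11 | +9,300 (18%); 0.08 |
| Residual correlation +0.5 | +27,900 (55%); 0.34 | +21,500 (43%); 0.24 | +15,000 (30%); 0.14 |
| Residual correlation −0.3 | −17,300 (−34%); 0.16 | −13,300 (−26%); 0.12 | −8,700 (−17%); 0.08 |

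**If the rule were applied to controls too.** A control who connects once a week uses the app on 12 of 84 days (14%), against the 59 needed to exceed 70%. Nearly all controls would be removed and the few left would be atypical, so this reading does not restore a randomised comparison.

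**The adherence wording over 84 days.**
- Every week: 5 × 12 = 60 days (71.4%). This already exceeds 70% (0.7 × 84 = 58.8, so 59 days), and joining the two rules admits nobody extra.
- Any single week: 5 of 84 days (6.0%) is enough. For a patient who uses the app on a random 40% of days, P(at least 5 of 7) = 0.096, so the chance of qualifying is 1 − (1 − 0.096)¹² = 0.70. Under the rule of more than 70% of all days it is about 0.

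**The case against.** Four arguments against the point carry weight.

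- **The analysis is supplementary.** Intention-to-treat is the main analysis, and nothing in the article gives the per-protocol result a confirmatory role. This stands. A reader might infer that the per-protocol result is there to rescue a null trial, but the text does not support that.
- **Keeping all controls is inferred.** This stands too, and the full protocol or SAP may settle it, so the silence alone is no defect. But the printed criterion works in one arm only, and neither way of handling controls yields a randomised comparison. That is a choice the article makes, not a detail it leaves out.
- **The joined rule is not clearly loose.** A reader might infer that one good week in 12 qualifies and that this adds to the bias. The Compliance section equates 70% with 5 of 7, so one threshold stated in two forms is the likelier intention. A looser rule would also exclude fewer patients and weaken the selection: at a correlation of +0.3 the bias falls from 17,200 to 9,300 counts/day as the share kept rises from 60% to 80%. What remains is an ambiguity of wording, separate from the bias.
- **Direction and size are assumed.** Correct. The article holds no data on adherence or its relation to activity, and zero or negative values cannot be ruled out.

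**Conclusion.** The point holds in limited form. Followed as written, the per-protocol comparison conditions on behaviour after randomisation that only one arm can show. It is therefore not a randomised comparison and can be biased. Upward bias is the more plausible direction, because motivation and good recovery are likely to raise both app use and activity, but the documents do not establish it. A flat statement that the analysis is biased toward benefit would go too far.

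The size of 13,000 to 15,000 counts/day, with type I error about 0.11, rests on three assumptions: 70% adherence, a correlation of 0.3 (beyond baseline for the lower figure), and all controls kept. The lower figure also assumes a baseline to follow-up correlation of 0.5. The primary result and the sample size are untouched. The plan should be changed, but the trial's main conclusion does not depend on it.

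**What to change.** 1. Define adherence once, over the whole period: app used on more than 70% of available days from discharge to week 12. Remove the weekly alternative.
2. Estimate the effect in adherers with a supportive complier-average analysis: two-stage least squares with randomised arm as instrument, adherence as treatment received, the same baseline covariates, and everyone randomised who has outcome data. Non-adherence is one-sided, since controls have no feedback app.
3. If a per-protocol comparison is still shown, state how controls are handled and label it descriptive.

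The cost is a few sentences and a few lines of code. The article reports the trial as recruiting at publication; the change should be made before any analysis by arm.

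There are two downsides. The confidence interval will be wider than that of the simple per-protocol estimate. The complier-average estimate also assumes that users below the threshold gain nothing. If they do benefit, it overstates the effect. For illustration, suppose 70% adhere with effect E and the rest gain half of it. Intention-to-treat is then 0.7E + 0.3 × 0.5E = 0.85E, and the estimate is 0.85E / 0.7 = 1.21E, which is 21% too high. State this assumption with the result.

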### Intervention

Two weeks prior to surgery and 12 weeks following discharge, patients will be equipped with a discrete patch and built-in accelerometer (SENS motion®, Denmark, Copenhagen) attached to the thigh of the leg not undergoing surgery. The patch will be worn 24 h a day, and there will be no need to remove the patch before the end of the study (2 + 12 weeks). Besides raw accelerometer counts (primary outcome measure), the accelerometer also measures daily activity, daily steps, and type of activity. Prior to this protocol, a pilot study evaluated the validity of the SENS accelerometer on a similar patient group, showing that SENS motion® can measure PA and differentiate between different types of activities, such as lying down, sitting, standing, and standing work [33]. Before discharge patients randomized to the intervention group will receive a tablet with the app (*“SENS motion”*). To simplify usage, the tablet only contains the "SENS motion" app.

Patients randomized to the intervention group will be motivated to be more physically active through elements of gamification (e.g. achieving step goals) and nudging (supporting notifications). The sensor will measure the PA of the patient and accelerometer counts, irrespectively of the type of activity, will be converted into daily steps, which will be visible to the patients. Through the app, patients will be able to choose between two user interfaces. Interface 1 (Fig. 3B) allows patients to view predefined goals, including locations in a self-selected city whereas Interface 2 (Fig. 3A) provides graphical representations of their daily activity and their history during the period they have worn the accelerometer. The graphical representations include daily steps, physically active minutes, and type of activity. The motivational intervention is reported and described using “The template for intervention description and replication” (TIDieR) [34].

Data from SENS motion sensors are encrypted directly on the sensor itself before being sent to the server. The data is stored pseudonymized with a user ID. The server is located in Germany, and for security reasons, the exact location cannot be disclosed.

